### **8.2.3. Techniques for Assessing Measurable Disease**

The same method and technique of assessment used at baseline should be used to characterize each identified and reported lesion during follow-up. Imaging-based evaluation is preferred to evaluation by clinical (physical) examination when both methods have been used to assess the antitumor effect of a treatment.

• Accepted methods of tumor assessment include: Clinical Examination: Clinical lesions will only be considered measurable when they are superficial (eg, skin nodules). Clinically detected lesions will only be considered measurable when they are superficial (eg, skin nodules) and the longest diameter is ≥2 cm. Palpable lymph nodes ≥2.0 cm should be demonstrable by CT scan.

• Chest X-ray (CXR): Lesions on CXR are acceptable as measurable lesions when they are clearly defined and surrounded by aerated lung. However, computerized tomography (CT) is preferable.

• CT, magnetic resonance imaging (MRI): Conventional CT and MRI should be performed with contiguous cuts of 10 mm or less in slice thickness. Spiral CT should be performed using a 5 mm contiguous reconstruction algorithm. This applies to tumors of the chest, abdomen, and pelvis. Head and neck and extremities require specific protocols as per RECIST.

**• Ultrasound:** Ultrasound should not be used to measure tumor lesions not clinically accessible when the primary endpoint is objective response. It is, however, a possible alternative to clinical measurements of superficial palpable nodes, subcutaneous lesions, and thyroid nodules. Ultrasound may be used to confirm the complete disappearance of superficial lesions usually assessed by clinical examination.

### **8.2.4. Objective Response Classifications**

The following RECIST criteria will be the primary method utilized in this trial for the assessment and reporting of tumor response data:

- Complete Response (CR): Disappearance of all target and non-target lesions. CR must be confirmed by repeat assessments performed no less than 4 weeks after the criteria for response are first met to qualify as CR;
- Partial Response (PR): At least a 30% decrease in the sum of the longest diameter (LD) of target lesions taking as reference the baseline sum LD. Non-target lesions may persist provided there is no unequivocal progression in these lesions.
- PR must be confirmed by repeat assessments performed no less than 4 weeks after the criteria for response are first met to qualify as PR;
- Progressive Disease (PD): At least a 20% increase in the sum LD of the target lesions from the smallest sum LD recorded since the beginning of therapy or the appearance of one or more new lesions or unequivocal progression of existing non-target lesions; and
- Stable Disease (SD): Measurements demonstrating neither sufficient shrinkage to qualify for PR nor sufficient increase to qualify as PD after the start of treatment taking as reference the smallest sum LD since the treatment started. During this time, non-target lesions may persist provided there is no unequivocal progression in these lesions.

### **8.2.5. Frequency of Tumor Measurements**

Tumor assessments will be performed every 6 to 8 weeks. CR and PR must be confirmed by repeat assessments performed 4-6 weeks after the criteria for response are first met to qualify as such response. Additional tumor measurements may be completed as needed.

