# 7. TRIAL PROCEDURES

The minimum required screening, on-study and follow-up evaluations are summarized in the following sections. Other parameters and/or increased frequency of examinations or clinical follow-up may be needed based on the findings during the trial.

Informed consent must be obtained from each patient being considered for the trial before any protocol-specified procedure is performed. In the event of scheduling conflicts, trial evaluations will take place on the designated day ± 3 days.

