**8.** The autoantibody panel will include antinuclear antibodies (ANA), antineutrophil cytoplasmic antibodies (ANCA), anti-DNA antibody (SS and DS), Rh factor (RhF), antithyroglobulin, anti liver-kidney microsomal (LKM), anti-islet-cell, antibodies to Ro (SSA) and to La (SSB) and antiphospholipid and/or other autoantibody tests.

**9.** Human anti-human antibody may be done at the Investigator’s discretion.

**10.** A total of 2000cGy to be delivered in 5 daily fractions using 6-18 MV photons.

**11.** Immune monitoring will be done using peripheral blood obtained by phlebotomy. PBMC and serum will be isolated and cryopreserved.

**12.** DNA extraction and banking for genomic evaluation.

**13.** Adverse event assessment to be performed continuously throughout the trial. Treatment-related adverse events will be followed until they resolve to baseline or Grade 1 or until the treating physician determines that they are irreversible.

**14.** Patients with measurable disease will be assessed by imaging every 8 weeks until progression (range 6-8 weeks). If a response is seen at week 8, the imaging will be repeated 4 weeks later. The same method of assessment and the same technique should be used for repeated measurements.

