## **8.2 Clinical response assessments**

All patients who have qualifying measurable disease outside the radiation field according to RECIST criteria, received investigational treatment, had baseline assessments and at least one on-study tumor assessment will be considered evaluable for response. Data on the response of the irradiated lesion will also be collected.

Tumor assessments will be performed at screening/baseline and then at 6-8 weeks following CP-675,206 dosing. Subjects exhibiting stable disease, partial response or complete response at the 8 week timepoint will undergo confirmatory re-evaluation 4-6 weeks following the first documented response. Patients may also be evaluated at 12 weeks following treatment. The same method of assessment and the same techniques used at screening must be performed.

Patients who were treated and removed from the trial prior to on-study tumor assessment for reasons such as patient request, lack of compliance, or as early toxicity (patients who went off study due to serious adverse events related to the trial drug therapy prior to reassessment of tumor lesions) will not be considered evaluable for the secondary objective of efficacy of the trial. Patients who discontinue treatment with stable disease or an unconfirmed response, who subsequently have a response confirmed prior to starting new treatment, will be classified as responders. If no confirmation is obtained, they will be considered as non-responders.

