### **8.2.6. Evaluation of Overall Response**

The best overall response is the best response recorded since the start of treatment until disease progression or recurrence (taking as reference for PD the smallest measurement since treatment started). For CR and PR the best response assignment will depend on the achievement of both the initial establishment and confirmation of CR or PR.

To be assigned a status of Partial Response (PR) or Complete Response (CR), changes in tumor measurements must be confirmed by repeat assessments that should be performed no less than 4 weeks after the criteria for response are first met, per RECIST.If a patient does not achieve a PR or CR but maintains Stable Disease (SD) for at least 10 weeks or more, then the best overall response for the patient will be SD.

| Overall Response | | | |
| --- | --- | --- | --- |
| Target Lesions | Nontarget lesions | New Lesions | Overall response |
| CR a | CR | No | CR |
| CR | Non-CR/Non-PD | No | PR |
| PR b | Non-PD | No | PR |
| SD c | Non-PD | No | SD |
| PD d | Any | Yes or No | PD |
| Any | PD | Yes or No | PD |
| Any | Any | Yes | PD |
| a, Complete Response  b, Partial Response  c, Stable Disease  d, Progressive Disease | | | |

##

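### Section 8.2.5 allows only 4-6 weeks for confirming a response, while Sections 8.2.4 and 8.2.6 set a 4-week minimum with no upper limit, so a late confirmation is scored differently by section

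*Protocol*

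**What the plan says.** The protocol states the timing of response confirmation in several places.

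- **Section 8.2.5 (Frequency of Tumor Measurements)** gives a window with two ends, worded as a qualifying condition: "CR and PR must be confirmed by repeat assessments performed 4-6 weeks after the criteria for response are first met to qualify as such response". It sets routine assessments at 6- to 8-week intervals and permits further measurements as needed.
- **Section 8.2.4 (Objective Response Classifications)** gives a minimum only: "PR must be confirmed by repeat assessments performed no less than 4 weeks after the criteria for response are first met to qualify as PR". The CR definition has the same minimum.
- **Section 8.2.6 (Evaluation of Overall Response)** repeats the minimum and attributes it to RECIST. A CR or PR "must be confirmed by repeat assessments that should be performed no less than 4 weeks after the criteria for response are first met".
- **Section 8.2 (Clinical response assessments)** says that patients with SD, PR or CR at week 8 "will undergo confirmatory re-evaluation 4-6 weeks following the first documented response". For patients who discontinue with stable disease or an unconfirmed response, it counts them as responders if a response is confirmed before new treatment starts. Otherwise: "If no confirmation is obtained, they will be considered as non-responders".
- **Table 2, note 14 (Section 7.2, repeated in Section 13)** sets imaging every 8 weeks with a range of 6-8 weeks, and adds: "If a response is seen at week 8, the imaging will be repeated 4 weeks later".
- **Section 7** provides that, where there is a scheduling conflict, "trial evaluations will take place on the designated day ± 3 days".

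**The concern.** Sections 8.2.4 and 8.2.5 both word their timing as a condition for being a CR or PR, and 8.2.6 makes best overall response depend on confirmation. The conditions differ for any confirmation obtained more than 6 weeks after the response is first seen, and nothing says which section governs. The routine imaging interval runs from 6 to 8 weeks, so it lies almost wholly in the region where the sections disagree.

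The choice of section decides who enters the best overall response listing (Section 10.5.1.1) and the duration of response analysis (Section 10.5.1.2). Section 2.4.3 notes that immune effects of radiation have been seen at both early and late timepoints, so a response first seen after week 8 is a case the plan should handle cleanly.

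A second, smaller problem sits at the other end of the window. Note 14 places the week-8 repeat exactly on the 4-week minimum, and the general visit tolerance can pull it below that minimum.

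**Working it through.** The plan has no figure to reproduce here. No power, alpha or sample-size calculation uses response, and Section 10.2 describes the sample size as empirical. The check compares intervals in days.

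**Inputs**
- Rule A (8.2.5): 4-6 weeks = 28 to 42 days.
- Rule B (8.2.4, 8.2.6): at least 4 weeks = 28 days or more.
- Routine gap between scans (8.2.5; Table 2 note 14): 6-8 weeks = 42 to 56 days, nominally 56 under note 14.
- Visit tolerance (Section 7): 3 days either way, for scheduling conflicts.

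**Step 1. Routine gap against each rule.** There are 56 − 42 + 1 = 15 possible whole-day gaps.
- Rule A is met by day 42 only: 1 of 15. If the 3-day tolerance is also applied to the upper end (42 + 3 = 45), days 42-45 qualify: 4 of 15.
- Rule B is met by all 15.

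These are counts of possible gaps, not probabilities. The protocol says nothing about how often each gap would occur.

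**Step 2. Particular cases, with no extra scan.**

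| First response seen | Next scan | Gap | Rule A (8.2.5) | Rule B (8.2.4, 8.2.6) |
|---|---|---|---|---|
| Week 8, repeat under note 14 | Week 12 | 4 weeks | met | met |
| Week 16, 8-week schedule | Week 24 | 8 weeks | not met | met |
| Week 14, 7-week schedule | Week 21 | 7 weeks | not met | met |
| Week 12, 6-week schedule | Week 18 | 6 weeks | met, at the limit | met |
| Week 12, at re-evaluation of week-8 SD | Week 16 | 4 weeks | met | met |

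The sections agree for a week-8 response repeated on time, for a 6-week schedule, and for a first response at week 12 followed by a week-16 scan. They disagree when the confirming scan comes more than 42 days after the first.

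**Step 3. The lower end.** Note 14 sets the repeat 4 weeks after the scan that showed the response. With the tolerance, the interval runs from 28 − 3 = 25 to 28 + 3 = 31 days. Days 25, 26 and 27 are below 28 and fail 8.2.4, 8.2.5 and 8.2.6 alike. Under Rule B the next routine scan can still confirm: week 16 is 56 days after week 8. Under Rule A it cannot, because 56 exceeds 42.

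**The case against.** The strongest reply is that 8.2.5 is itself an instruction about scan frequency. Read that way, it orders a repeat at 4-6 weeks after any first CR or PR, whenever seen, and it allows additional measurements. Note 14 describes the week-8 case without forbidding a repeat later. A scan done at 4-6 weeks satisfies 8.2.4, 8.2.5 and 8.2.6 together, so the sections part only when that repeat is not done in time. This stands as a limit on the point: the schedule does not by itself make later responses unconfirmable. It does not remove the conflict. Additional measurements are optional, the schedule table specifies the early repeat only for week 8, and a repeat obtained after 6 weeks still has two classifications.

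Stronger readings that a reader might infer are not supported:

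- **That every response after week 8 misses the window.** The 6-week schedule and the week-12 case both meet both rules.
- **That Section 8.2 also makes 4-6 weeks a condition to qualify, and scores late confirmations as non-response.** There, 4-6 weeks is an instruction about when to re-evaluate. The non-responder sentence concerns patients who discontinue, and the sentence before it accepts confirmation at any time before new treatment. Section 8.2 therefore sits closer to 8.2.4 and 8.2.6.
- **That one can state how often the week-8 repeat will be too early.** The tolerance applies only to scheduling conflicts, note 14 counts from the response scan, Table 2 has no imaging mark at D85, and no distribution of visit days is given.
- **That a specific loss in response rate follows.** The number of response-evaluable patients is not stated. The response rates quoted in Section 2.3.3.3 come from repeated dosing in metastatic melanoma, a different setting.

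The point about importance also stands. Section 2.5 says the trial is designed to provide safety data and the phase II dose, and leaves efficacy to phase II.

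**Conclusion.** The inconsistency is real. A CR or PR confirmed more than 42 days after it is first seen counts as confirmed under 8.2.4 and 8.2.6 and as unconfirmed under 8.2.5, with no rule of precedence. If no extra scan is done, this covers most later responses followed on the routine schedule: 14 of the 15 possible gaps, or 11 of 15 if the 3-day tolerance is applied to the upper limit. Separately, a week-8 repeat moved forward because of a scheduling conflict can fall at 25-27 days and fail all three sections.

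The effect is confined to the descriptive secondary response endpoints, best overall response and duration of response. DLT assessment, MTD determination and sample size are untouched. How many patients would be reclassified cannot be derived from the protocol. It is worth correcting because it leaves open who counts as a responder, and the correction is nearly free.

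**What to change.** 1. Use one qualifying rule in Sections 8.2, 8.2.4, 8.2.5 and 8.2.6: CR or PR is confirmed by a repeat assessment at least 28 days after the response is first documented and before any new treatment.
2. In 8.2 and 8.2.5, keep 4-6 weeks only as the target time for the repeat scan, and remove it from 8.2.5 as a condition to qualify.
3. State that the confirmatory scan may not be earlier than 28 days after the first, so the general 3-day tolerance cannot shorten it.
4. If the 6-week upper limit is kept instead, extend note 14 (in both copies of Table 2) to a response first seen at any scan, so that the schedule delivers the scan the rule needs.

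The cost is protocol wording. Under the at-least-28-day rule no additional scan is needed to qualify, because every routine gap of 42-56 days can confirm. Keeping the 6-week limit would cost at most one additional repeat scan per late responder.

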### **8.2.6. Evaluation of Overall Response**

The best overall response is the best response recorded since the start of treatment until disease progression or recurrence (taking as reference for PD the smallest measurement since treatment started). For CR and PR the best response assignment will depend on the achievement of both the initial establishment and confirmation of CR or PR.

To be assigned a status of Partial Response (PR) or Complete Response (CR), changes in tumor measurements must be confirmed by repeat assessments that should be performed no less than 4 weeks after the criteria for response are first met, per RECIST.If a patient does not achieve a PR or CR but maintains Stable Disease (SD) for at least 10 weeks or more, then the best overall response for the patient will be SD.

| Overall Response | | | |
| --- | --- | --- | --- |
| Target Lesions | Nontarget lesions | New Lesions | Overall response |
| CR a | CR | No | CR |
| CR | Non-CR/Non-PD | No | PR |
| PR b | Non-PD | No | PR |
| SD c | Non-PD | No | SD |
| PD d | Any | Yes or No | PD |
| Any | PD | Yes or No | PD |
| Any | Any | Yes | PD |
| a, Complete Response  b, Partial Response  c, Stable Disease  d, Progressive Disease | | | |

##

## **8.3 Immunological monitoring**

Immunological monitoring will be done on peripheral blood mononuclear cells (PBMC) and serum using methods such as flow cytometric analysis and ELISA, respectively. Immunological responses will be evaluated at baseline and at 1, 2, 4, 8 and 12 weeks following CP-675,206 dosing. Additional time points may also be evaluated at the Investigator’s discretion. Samples will be cryopreserved until analysis.

The relative proportion of various T cell subsets in PBMC obtained by phlebotomy will be monitored by flow cytometry, as well as the expression of lymphocyte activation markers. For HLA-A*0201+ subjects, further assessments may be done in order to evaluate the frequency of T cells specific for defined breast tumor antigens. This may be done using MHC-peptide multimers and/or ELISpot assays. PBMC obtained from similar patients receiving irradiation alone will also be assayed to provide information on the immunological effect of irradiation alone. Serum will also be collected for monitoring responses to the investigational treatment, such as alterations in circulating cytokine levels or markers for epithelial cell apoptosis/necrosis by ELISA.

# 9. ADVERSE EVENT REPORTING

This study will utilize the CTCAE 3.0 for toxicity and Adverse Event reporting. A copy of the CTCAE 3.0 can be downloaded from the CTEP home page (http://ctep.cancer.gov). All appropriate treatment areas should have access to a copy of the CTCAE 3.0.

This study will be monitored by the Princess Margaret Hospital Data Safety Monitoring Board.

## **Reporting requirements**

Within one (1) working day, report by **telephone** to the Principal Investigator or research nurse serious adverse events as defined below.These events should also be reported within three (3) working days, in **writing**, to the Principal Investigator. An appropriate adverse event form should be used.

*Associated with the use of the drug/biologic*: There is a reasonable possibility that the experience may have been caused by the drug/biologic.

*Life threatening adverse drug/biologic experience*: Any adverse drug/biologic experience that places the subject, in the view of the investigator, at immediate risk of death from the reaction as it occurred.

*Serious adverse drug/biologic experience*: Any adverse drug/biologic experience occurring at any dose that results in any of the following outcomes:

- Death (including all deaths within 30 days of the last administration of study drug/biologic.

- A life-threatening adverse drug/biologic experience

- Inpatient hospitalization or prolongation of existing hospitalization

- A persistent or significant disability/incapacity

- A congenital anomaly/birth defect

- Any other medical event that, in appropriate medical judgment, may require medical or surgical intervention to prevent one of the outcomes listed above.

*Unexpected adverse drug/biologic experience*: Any adverse drug/biologic experience, the specificity or severity of which is not consistent with the product monograph, or not consistent with the risk information described above as a protocol-specific expected adverse event (see “Expected Adverse Events and Protocol-Specific Expedited Adverse Event Reporting Exclusions”, above).

Qualifying serious adverse events must be reported to the UHN Research Ethics Board (REB) according to the UHN REB’s required timeframe.

The Sponsor (IND/CTA holder) will be responsible for reporting all adverse events to the appropriate regulatory agencies (e.g. REB/Health Canada as applicable) as per each agencies individual reporting requirements and within each agencies required timeframe.

Data on all adverse experiences/toxicities (excluding fever and hematologic toxicities), regardless of seriousness must be collected for documentation purposes only. AEs should be followed for 6 weeks after the last dosing of study drug/biologic.

Non-serious adverse events will be reported to the appropriate regulatory agencies (e.g. REB/Health Canada as applicable) at the time of the annual report if required by that agency.

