## **4.4. Dose Limiting Toxicities**

Adverse events and other symptoms will be graded according to the NCI Common Terminology Criteria for Adverse Events version 3.0. (<http://ctep.cancer.gov/reporting/ctc.html>).

Dose-limiting toxicity (DLT) is defined as any of the following when considered related to CP-675,206 therapy:

1. • Any CTC Grade 4 treatment related toxicity of any duration.
2. • Other Grade 3 or greater toxicities that do not recover to ≤ Grade 1 or baseline within 7 days of maximal management
3. • Grade 2 or greater treatment related clinical autoimmune toxicity of critical organs, which are defined as lung, heart, kidney, bowel, bone marrow and nervous system, including the eye (except anterior uveitis).

Assessment of DLTs during the first 12 weeks after CP-675,206 dosing will be completed to determine the next dose level.

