### **6.1.4. Management of CP-675,206 Toxicity**

CP-675,206 is an immune modulator, so Investigators should be alert for the development of immune-mediated side effects.

The majority of the adverse events reported in early phase trials have been manageable and well tolerated. The most common treatment-emergent, treatment-related adverse event is diarrhea. Diarrhea typically developed 1 to 2 months after the first dose of CP-675,206 (range: 4-72 days).

Although CP-675,206 is a fully human monoclonal antibody, immunogenicity remains a possibility, and thus acute hypersensitivity reactions such as urticaria, pruritus, laryngeal edema, angioedema, bronchospasm, respiratory distress, nausea, vomiting, abdominal cramps and pain, acute back pain, fever, diarrhea, hypotension and fatal anaphylactic shock, as well as sub acute reactions, are also possible. Possible immune-mediated disorders observed involve the skin (vitiligo and cutaneous leukocytoclastic vasculitis), the thyroid gland (autoimmune thyroiditis), the liver (autoimmune hepatitis), the pituitary (hypophysitis) and bone marrow (immune thrombocytopenic purpura). Abnormal lab results that may be immune-mediated include elevations of serum lipase and amylase and liver function tests. There has been one report of treatment-related uveitis, which resolved within 48 hours after treatment with topical steroids. Across all studies, toxicities generally recovered within 12 weeks, allowing continuation of treatment.

If a patient has an adverse event that is thought to be potentially immune-mediated (other than vitiligo), the Investigator should send a blood sample for autoimmune antibody testing.

CP-675,206 is a monoclonal antibody of the IgG2 type, and it is expected that it would cross the placenta if administered to a pregnant woman and could be secreted in breast milk of a lactating woman. The effect of exposure of a fetus or newborn to CP-675,206 is unknown. Women of childbearing potential must agree to use contraception during this trial and for 12 months after the last dose of CP-675,206.

*Note:* In general, it is not expected that the combination of CP-675,206 with this radiation dose will increase CP-675,206-related toxicities. However, radiation of the sites that are the most common autoimmune targets following CP-675,206 administration will be avoided when possible.

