**Table 2. On-trial assessments**

**Test/Assessment: Study Day Number:**

|  | D1 | D2 | D3 | D4 | D5 | D8  (1w) | D15  (2w) | D22  (3w) | D29  (4w) | D43  (6w) | D57 (8w) | D71  (10w) | D85  (12w) |
| --- | --- | --- | --- | --- | --- | --- | --- | --- | --- | --- | --- | --- | --- |
| Weight |  |  | X |  |  | X | X | X | X | X | X | X | X |
| Physical Exam, including signs of autoimmunity |  |  | X1 |  |  | X | X | X | X | X | X | X | X |
| ECOG status |  |  | X1 |  |  | X | X | X | X | X | X | X | X |
| Hematology2,3,4 | X |  |  |  |  | X | X | X | X | X | X | X | X |
| Serum Chemistry3,4,5 | X |  |  |  |  | X | X | X | X | X | X | X | X |
| Microscopic or Dipstick Urinalysis3,4,6 | X |  |  |  |  | X | X | X | X | X | X | X | X |
| Thyroid Function3,4,7 |  |  |  |  |  |  |  |  | X |  |  |  | X |
| Autoantibody Panel3,4,8 | X |  |  |  |  |  |  |  | X |  |  |  | X |
| Human anti-human antibody (HAHA)9 | X |  |  |  |  |  |  |  | X |  |  |  | X |
| Radiation10 | X | X | X | X | X |  |  |  |  |  |  |  |  |
| CP-675,206 Administration |  |  | X |  |  |  |  |  |  |  |  |  |  |
| Immune Monitoring11 | X |  |  |  |  | X | X |  | X |  | X |  | X |
| Blood specimen for genomic analysis12 | X |  |  |  |  |  |  |  |  |  |  |  |  |
| AE Monitoring13 | X | X | X | X | X | X | X | X | X | X | X | X | X |
| Tumor Imaging (CT, MRI)14 |  |  |  |  |  |  |  |  |  |  | X |  |  |

**1.** Tests performed/specimens drawn prior to dosing with CP-675,206.

**2.** Hemoglobin, WBC with 5-part differential (percent and absolute values), platelet count

**3.** Clinically significant abnormalities should be reported as Adverse Events in the CRF.

**4.** Assessments may be performed within 24 hours of the designated timepoints.

**5.** Calcium, chloride, total protein, potassium, random glucose, sodium, blood urea nitrogen/BUN, creatinine, AST/SGOT, ALT/SGPT, alkaline phosphatase/ALP, lactic acid dehydrogenase/LDH, amylase, lipase, albumin, total bilirubin

**6.** Complete urinalysis (with microscopic analysis of centrifuged sediment for casts or other abnormalities); performed at baseline. In subsequent evaluations, dipstick urine testing is allowed in lieu of microscopic analysis, however, microscopic analysis must be performed if dipstick results are abnormal.

**7.** Thyroid stimulating hormone (TSH), T3, T4. Thyroid function tests are also done as part of the pre-trial assessments (within 14 days before treatment begins).

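### Section 9.2 excludes fever and hematologic toxicities from adverse event collection, contradicting the DLT definition, Table 2 and the primary safety analysis

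*Protocol*

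**What the plan says.** Protocol section 9.2 (Reporting requirements) sets the scope of general adverse event collection in one sentence: "Data on all adverse experiences/toxicities (excluding fever and hematologic toxicities), regardless of seriousness must be collected for documentation purposes only".

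Four other places bear on the same data:

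- **Section 4.4** defines DLTs, subject to relatedness to CP-675,206, by three criteria. The first is "Any CTC Grade 4 treatment related toxicity of any duration". The second is "Other Grade 3 or greater toxicities that do not recover to ≤ Grade 1 or baseline within 7 days of maximal management". The third is clinical autoimmune toxicity of Grade 2 or above in critical organs, "which are defined as lung, heart, kidney, bowel, bone marrow and nervous system". None of them carves out fever or hematologic events.
- **Section 6.1.4** lists immune thrombocytopenic purpura, under bone marrow, among the possible immune-mediated disorders already observed with the drug.
- **Table 2, note 3** (section 7.2, repeated in section 13) is attached to the hematology row and reads "Clinically significant abnormalities should be reported as Adverse Events in the CRF".
- **Section 10.4.1** makes the type, frequency, severity, timing and relationship of adverse events, together with laboratory abnormalities, the analysis of the primary endpoint.

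**The concern.** The excluded class overlaps with the class that can stop escalation. A site following section 9.2 and a site following Table 2 would build different adverse event data sets from the same patients. The two instructions also differ in force: section 9.2 uses a mandatory verb and excludes, while note 3 uses a recommendation that depends on a judgement of clinical significance. Note 3 is attached only to laboratory rows, so it does nothing for fever.

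At stake are the completeness of the primary safety data and the counts that decide escalation and the MTD. Those counts are taken over 3 or 6 patients, so a single event matters.

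**Working it through.** **1. Which events fall under both section 9.2 and section 4.4?** The exclusion is unqualified, so every grade is covered. Setting it against the three DLT criteria, and given relatedness:

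| DLT criterion (4.4) | Event inside the 9.2 exclusion that could meet it |
| --- | --- |
| Any related Grade 4 | A Grade 4 blood count |
| Other Grade 3 or above, not recovered in 7 days | A prolonged Grade 3 cytopenia or fever |
| Clinical autoimmune, Grade 2 or above, critical organ | Autoimmune cytopenia, bone marrow being named |

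**2. Which other routes would still catch them?**

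- *Scheduled hematology.* Table 2 has counts on D1 and eight later visits (D8, D15, D22, D29, D43, D57, D71, D85), with none on D2 to D5. Note 3 then asks for clinically significant abnormalities as adverse events.
- *Continuous adverse event assessment.* Table 2, note 13, with no exclusion stated.
- *Serious event reporting.* Section 9.2, with no exclusion for fever or hematology in the definition of serious.
- *Separate DLT assessment.* Section 4.4 requires it over the first 12 weeks, to set the next dose level.
- *Infusion monitoring.* Sections 6.2.2 and 7.2 cover temperature and treatment-emergent events during the infusion, and section 6.2.2 extends monitoring to about one hour after it.

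**3. What is left?** Hematologic events that could be DLTs but are not serious, such as a Grade 2 or 3 autoimmune cytopenia or a Grade 4 count not judged serious. They depend on which instruction the site follows. Non-serious fever outside the infusion period is also left, and no laboratory note covers it.

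**4. What does one missed DLT do under section 4.2?**

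- 1/3 recorded as 0/3: escalate instead of expanding the cohort.
- 2/6 recorded as 1/6: escalate instead of stopping. Under section 4.5, 1/6 is also compatible with calling that dose the MTD.

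**5. How does this bear on the section 10.3 table?** For a true DLT rate p, escalation on 0/3 or 1/6 has probability

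P(p) = (1−p)³ + 3p(1−p)² × (1−p)³.

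For p = 10% to 90% this gives 0.906, 0.709, 0.494, 0.309, 0.172, 0.082, 0.032, 0.009 and 0.001. All nine printed figures reproduce, so the table is right. It presumes that every DLT is counted.

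If a share f of DLTs went unrecorded, p is replaced by p(1−f). The protocol gives no f, so the values below are assumptions that show direction only. At p = 40%:

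- f = 0: 0.309
- f = 10%, effective rate 36%: 0.378
- f = 25%, effective rate 30%: 0.494
- f = 50%, effective rate 20%: 0.709

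Here f is a share of all DLTs. Nothing in the protocol says what fraction of DLTs would be hematologic or febrile, so none of these values is an estimate for this trial.

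**The case against.** The strongest reply is that section 9.2 governs reporting and does not amend section 4.4. DLT assessment has its own 12-week instruction, sections 4.2 and 6.1.1 tie escalation to DLTs observed over those 12 weeks, and the other routes listed above all remain. This largely stands. A reader might infer that whole classes of DLTs are absent from the data that drive escalation, or that fever is lost. The protocol does not support that, because no passage says that the section 9.2 data set alone drives escalation.

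A reader might also try to size the loss from section 2.3.2.1, where fever and anemia each occurred in 11.4% of 44 single-agent patients (5/44). Applied to 30 patients that is 0.114 × 30 = 3.4 for each event, with none shown in the report. This does not hold either. Those rates are all-causality and not limited by grade. Section 10.4.1 includes laboratory abnormalities, so anemia would still appear. The same section lists related Grade 3 events as diarrhea, rash, raised lipase and asthma only, and attributes no Grade 4 event to the drug. That is 0 of 44 patients with a related Grade 3 or 4 hematologic or fever event.

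Finally, the documentation-only phrase might be read as barring these data from analysis. It sits among reporting rules and is followed by a sentence leaving non-serious events to the annual report, so the more natural meaning is collection without expedited reporting.

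The reply does not remove the contradiction. Note 3 and section 9.2 give opposite instructions for hematology, and the serious event route does not catch non-serious DLTs.

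**Conclusion.** The protocol contradicts itself on whether fever and hematologic toxicities enter the adverse event data, and section 9.2 is wrong as written. The consequence is possible inconsistent or missed recording, confined mainly to non-serious hematologic events that could qualify as DLTs and to non-serious fever outside the infusion.

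The effect per event is clear: one missed DLT can reverse a cohort decision. How often that would happen cannot be stated. The protocol gives no rate for related hematologic or febrile DLTs; section 6.1.4 shows that an immune hematologic event is possible, without a frequency. The conclusion rests on reading the exclusion literally, as a site could. It does not require that the other recording routes fail altogether.

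**What to change.** - In section 9.2, delete the parenthesis that excludes fever and hematologic toxicities.
- State there that all adverse events, including fever and hematologic events, are recorded, graded by CTCAE 3.0, and available both for DLT assessment under section 4.4 and for the section 10.4.1 analysis.
- Reword the documentation-only phrase so that it plainly means these events are not subject to expedited reporting.
- Reconcile section 9.2 with section 4.4, Table 2 note 3 (both printings) and section 10.4.1, so that one rule governs what enters the CRF.

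The cost is wording and slightly more adverse event data entry. No new blood draws are needed, since hematology is already scheduled on D1 and at eight later visits through D85.
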